### Principles of the analyses

All analyses within the scope of the SPIZ evaluation are carried out in the intention-to-treat population. Missing values are identified, and their underlying mechanisms are examined in terms of randomness. When values are missing, the individuals in question are excluded from the respective sub-analyses. The results of the evaluation are published in full, transparently, and independently of the outcome of the evaluation. The method chapter is based on the SPIRIT reporting guidelines [22]. Reporting is based on the CONSORT and TIDieR guidelines [23, 24].

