### Enrollment, randomization and patient pathway

After enrollment, which takes place not later than eight days following discharge from the primary inpatient stay for cellular therapy, patients are randomly assigned in a 1:1 ratio to either the SPIZ program or the control group. The randomization is stratified according to patient age (< 60 years or ≥ 60 years) for each of the three cellular therapy centers individually using the REDCap (Research Electronic Data Capture)-based project database. Prior to the commencement of the study, age-group-specific randomization lists have been created through block randomization, employing permuted blocks of variable length. These randomization lists are prepared by the Dresden Coordination Center for Clinical Trials, which is also responsible for the preparation and administration of the REDCap project database. The randomization result is displayed to study staff in REDCap once informed consent and eligibility based on the inclusion and exclusion criteria have been documented. Depending on group allocation, patients proceed through either the SPIZ pathway or standard routine care (Fig. 2). Patients are scheduled to receive treatment for a minimum duration of 12 months and a maximum duration of 24 months.

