### Sample size

Sample size calculation for the primary study population is based on the primary endpoint. The literature available at the time of sample size planning showed that there was a rehospitalisation rate of 55% after alloHCT in a German population [10]. Given that deceased patients were typically hospitalised beforehand, it can be inferred that the 55% figure accurately represents the routine clinical care. The SPIZ program should reduce the mortality or disease-specific rehospitalisation rate to 35% or less. The case number calculation was performed with a one-sided Fisher test. Given a significance level of 5% and a yielded power of 80%, it is assumed that 143 patients in the intervention group and 143 patients in the control group are required (calculated with GPower 3.1). With an estimated drop-out rate of 5%, 302 patients must be included.

While disease- and cell therapy-specific rehospitalization or death includes all complications typically associated with the underlying hematological condition or cell therapy, other reasons for rehospitalization or death are defined as independent, e.g., joint replacement due to arthrosis, or an accident. The analysis of the primary endpoint will be conducted one year after primary hospital discharge of the last enrolled patient. Death or rehospitalization are considered equivalent primary endpoints.

Recruitment of health care providers involved in SPIZ (secondary study population) for twelve qualitative interviews starts 18 months after initiation of patient enrollment.

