### Data analysis regarding primary hypothesis and secondary hypothesis a)

The confirmatory test of the primary outcome at 12 months will be performed using Fisher’s exact test. All outcomes of secondary hypothesis a) are presented descriptively for the intervention and control groups according to the respective survey dates. The same applies to the primary combined outcome at time points 6, 18, and 24 months. Metric values will be compared between groups in terms of their means or, in the case of skewed distributions, their medians; categorical values will be compared in terms of their distributions. For events (death/ complication/ hospitalisation), survival time analyses and hazard ratios will be calculated. Logistic or Poisson regressions will be used to estimate effect size measures (odds ratios or relative risks). In addition, the control and intervention groups will be compared with regard to potential confounders. Should serious biases occur despite randomization, these will be addressed as appropriate through adjustments, subgroup analyses, or sensitivity analyses.

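### Complete-case exclusion is the only missing-data rule, with no exception or sensitivity analysis for the 12-month Fisher test, and it leaves the 18- and 24-month composite proportions undefined for patients with short follow-up

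*Protocol article*

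**What the plan says.** Under *Principles of the analyses* the protocol article sets the population: "All analyses within the scope of the SPIZ evaluation are carried out in the intention-to-treat population". It then says that missing values will be identified and their mechanism examined for randomness, and gives one handling rule: "When values are missing, the individuals in question are excluded from the respective sub-analyses". That rule does not depend on what the examination shows. The section names no other method and makes no exception for the primary endpoint.

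The section *Data analysis regarding primary hypothesis and secondary hypothesis a)* fixes the primary analysis as follows: "The confirmatory test of the primary outcome at 12 months will be performed using Fisher’s exact test". For the descriptive presentation at other times it adds: "The same applies to the primary combined outcome at time points 6, 18, and 24 months". It also plans time-to-event work: "For events (death/ complication/ hospitalisation), survival time analyses and hazard ratios will be calculated".

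On loss and length of follow-up, the *Sample size* section states: "With an estimated drop-out rate of 5%, 302 patients must be included". The section *Enrollment, randomization and patient pathway* gives the duration per patient: "Patients are scheduled to receive treatment for a minimum duration of 12 months and a maximum duration of 24 months". The *Results* section gives first enrolment on 16 January 2024, last enrolment on 29 January 2026, and 153 patients per group.

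**The concern.** Fisher's exact test needs a yes/no status for each patient. If the stated rule governs it, randomised patients who leave event-free before 12 months drop out of the confirmatory comparison. That sits badly with a claim that every analysis is by intention to treat. Patients know their allocation and the programme is intensive, so reasons for leaving may differ between arms and may be related to prognosis. Examining the mechanism of missingness does not help if exclusion follows whatever is found.

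The 18- and 24-month composite raises a different problem. By design, many patients will not have been followed that long when the data are cut. An early death or rehospitalisation settles a patient's 24-month status even with 13 months of follow-up, whereas an event-free patient with 13 months has no 24-month status. The text does not say whether the exclusion rule removes only the second kind of patient or both. The first reading inflates the reported proportions; the second does not.

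**Working it through.** **The plan's drop-out step.** 143 / 0.95 = 150.5, rounded up to 151 per arm, 302 in total; this reproduces. Inflating for drop-out implies that drop-outs are expected not to contribute to the primary analysis, which fits the exclusion rule being meant for it.

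**Primary test: power.** Inputs: 55% against 35%, one-sided 5% (the planning section says "The case number calculation was performed with a one-sided Fisher test"), 153 per arm, 5% loss. 0.05 × 153 = 7.65, about 8 per arm, leaving 145. Exact power of the one-sided Fisher test is 96.1% at 153 per arm and 95.9% at 145, so the loss in power is negligible. (At 143 per arm it is 95.6% rather than the stated 80%. That is a separate matter.)

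**Primary test: bias.** The observed counts below are assumed. The worst case gives all 8 missing SPIZ patients an event and the 8 missing controls none; the best case reverses this.

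| Observed, control vs SPIZ | Handling | Difference | One-sided p |
|---|---|---|---|
| 80/145 vs 51/145 (planned effect) | complete cases | 20.0 points | 0.0005 |
| | worst: 80/153 vs 59/153 | 13.7 points | 0.011 |
| | best: 88/153 vs 51/153 | 24.2 points | <0.0001 |
| 80/145 vs 58/145 (smaller effect) | complete cases | 15.2 points | 0.007 |
| | worst: 80/153 vs 66/153 | 9.2 points | 0.068 |

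For the smaller effect, with no events among the missing controls, p is 0.043 if 6 of the 8 missing SPIZ patients had an event and 0.054 if 7 did. The conclusion changes only near the extreme.

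**Follow-up at 18 and 24 months.** Accrual from 16 January 2024 to 29 January 2026 is 744 days. Assume even accrual. The share able to reach m months is (days from first enrolment to cut-off − 30.4375 × m) / 744.

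- Cut-off 29 January 2027 (last enrolment plus 12 months): 24 months, (1109 − 730.5) / 744 = 50.9%, so 49.1% cannot; 18 months, (1109 − 547.9) / 744 = 75.4%, so 24.6% cannot.
- Cut-off 30 June 2027: 24 months, (1261 − 730.5) / 744 = 71.3%, so 28.7% cannot; 18 months, (1261 − 547.9) / 744 = 95.8%, so about 4% cannot.

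**Size of the inflation if only event-free short-follow-up patients are dropped.** Assume F(t) = 1 − (1 − p)^((t/12)^k), with p the 12-month rate (55% or 35%) and k = 1, 0.5 or 0.3. With r the share reaching m months and G the average of F over the follow-up times of the rest, the reported proportion is [r·F(m) + (1 − r)·G] / [r + (1 − r)·G].

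Worked for k = 1, m = 24, r = 0.509:

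- Control: F(24) = 1 − 0.45² = 0.798; G = 1 − (0.45 − 0.2025)/0.7985 = 0.690; reported (0.509 × 0.798 + 0.491 × 0.690) / (0.509 + 0.491 × 0.690) = 0.878.
- SPIZ: F(24) = 1 − 0.65² = 0.578; G = 1 − (0.65 − 0.4225)/0.4308 = 0.472; reported 0.710.

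| 24 months, cut-off 29 January 2027 | Control true → reported | SPIZ true → reported | Difference true → reported |
|---|---|---|---|
| k = 1 | 79.8% → 87.8% | 57.7% → 71.0% | 22.0 → 16.9 points |
| k = 0.5 | 67.7% → 79.8% | 45.6% → 61.0% | 22.1 → 18.8 points |
| k = 0.3 | 62.6% → 76.2% | 41.2% → 57.1% | 21.4 → 19.1 points |

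At 18 months the inflation is about 5 to 7 points per arm. With data to 30 June 2027 it is about 5 to 8 points at 24 months and about 1 point at 18 months.

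If instead everyone without enough potential follow-up is set aside, whatever their event status, F(m) is recovered under independent administrative censoring, at the price of about half the sample at 24 months.

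**The case against.** The rule speaks of sub-analyses and does not name the confirmatory test. Intention to treat settles which arm a patient is counted in; what to do about an unobserved outcome is a further question. A patient who died or was rehospitalised before leaving has a known composite status, so nothing is missing. The 18- and 24-month figures are descriptive, survival analyses that handle censoring are already planned, and imputation details usually sit in a statistical analysis plan, which exists but is not shown.

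Much of this stands. Applying the rule to the Fisher test is an inference, though a fair one, since no other rule is given and the sample size is inflated for drop-out. Complete-case exclusion is better called a weakness beside the intention-to-treat statement than a flat contradiction of it. What does not stand is that this is only missing detail: the article states a rule and makes it unconditional. The sensitivity analyses it mentions elsewhere concern confounder imbalance despite randomisation, not missing outcomes. The survival analyses are listed beside the 18- and 24-month proportions, not in their place.

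A reader might infer that the primary test is compromised because about half the patients cannot reach 24 months. The documents do not support that. The primary analysis comes a year after the last patient's discharge and minimum follow-up is 12 months, so administrative cut-off leaves the 12-month test untouched.

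**Conclusion.** The point holds as a should-fix. For the primary test, the only stated rule excludes patients with missing status, and no sensitivity analysis for missing outcomes accompanies it. At 5% loss the effect on power is negligible. The planned effect survives even the worst case (p = 0.011), while a smaller effect of about 15 points would not (0.007 to 0.068). These figures assume a one-sided 5% test, 8 missing per arm, the illustrative counts and an extreme pattern of loss; they bound the risk and do not predict it.

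For the later time points, roughly 25% (18 months) and 49% (24 months) of patients cannot be fully followed, falling to 4% and 29% if data run to 30 June 2027. Even accrual and both cut-offs are assumptions, since the article dates only the primary analysis.

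It would be going too far to say that the 18- and 24-month proportions will be biased. The 8- to 16-point inflation at 24 months arises only if early events are kept while event-free patients with short follow-up are dropped, and the article does not say so. Nor would it favour the intervention: both arms rise and, in the scenarios above, the difference between them shrinks.

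**What to change.** Keep Fisher's exact test as the primary test, and replace the general exclusion sentence with rules for the composite:

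1. Any adjudicated primary-endpoint event before loss to follow-up counts as an event at 12 months.
2. Patients lost event-free before 12 months are retained through multiple imputation by arm, at least as a prespecified sensitivity analysis. Fisher p-values do not pool directly, so report a pooled risk difference or relative risk beside the test.
3. A tipping-point analysis shows how many missing patients in each arm would need an event for the conclusion to change, as in the counts above.
4. The 18- and 24-month composite is reported as Kaplan-Meier estimates by arm with confidence intervals, taken from the survival analyses already planned, with the data cut-off date and numbers at risk stated.

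The cost is a change of wording and modest programming, with no new data. First results are expected in mid-2027, and the change should be made and dated before outcome data are compared by arm.

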## Results

The study was approved by the institutional review board of the Medical Faculty of TUD Dresden University of Technology (BO-EK-408092023), the institutional review board of the Medical Faculty of Leipzig University (405/23-lk X), and the Chamber of Physicians of Saxony (EK-BR-130/23 − 1). The study has been registered in the German Clinical Trials Register (DRKS-ID: DRKS00034454). Written informed consent was obtained from all participants. The study is conducted in accordance with the World Medical Association Declaration of Helsinki. A study-specific data protection concept has been developed and implemented. Any protocol amendments will be registered in the German Clinical Trials Register.

Following the establishment of the required study personnel and infrastructure at the three cell therapy centers, the first patient was enrolled on January 16, 2024. After a recruitment period of two years, enrollment was completed on January 29, 2026. To allow sufficient time for patient training regarding the SMILe App and usage of video consultations in the intervention group, patients were usually enrolled and randomized several days prior to the anticipated discharge. Therefore, usually some time elapsed until study commencement, which was scheduled at the first outpatient visit. Upon reaching the planned sample size of 302 patients, we observed that only 149 intervention group patients reached study commencement, compared to 153 patients in the control group. Recruitment was therefore continued according to the randomization lists, finally leading to 153 patients in each group, respectively. Given the minimum post-treatment follow-up period of 12 months, the first study results are expected in mid-2027.

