Fidelity measures include successful app onboarding, the frequency of app entries and data reviews, the number and type of case management contacts, home visits and video consultations, participation in case conferences, completion of scheduled assessments, and deviations from the planned intervention pathway. As the intensity of several components is tailored to participants’ clinical needs, no minimum number of home visits, video consultations, or case conferences is required. Intervention delivery is considered to have commenced once the participant has completed SPIZ onboarding, is discharged from index hospitalization, and has used at least one component of the SPIZ intervention. To minimize contamination, the SPIZ-specific components are organized separately and provided only to participants allocated to the intervention group. Control-group participants are not enrolled into the SMILe App, assigned to a SPIZ case manager, proactively monitored by the onco nurses, or included in protocol-specific home visits, video consultations, or case conferences. Clinically necessary care will never be withheld from either group. All potential primary endpoint events will be adjudicated by two board-certified hematologists who are blinded to treatment allocation. Any disagreements will be resolved by consensus or, if necessary, by a third board-certified hematologist who is also blinded to treatment allocation.

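### Accrual was counted and topped up on patients who reached study commencement after randomization, which conflicts with the promised intention-to-treat analysis

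*Protocol article*

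**What the plan says.** All places are in the protocol article.

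- **Timing (Results).** To leave time for app training, "patients were usually enrolled and randomized several days prior to the anticipated discharge". Study commencement came later, at the first outpatient visit.
- **Counting (Results).** When the planned 302 was reached, "we observed that only 149 intervention group patients reached study commencement, compared to 153 patients in the control group". The next sentence reads: "Recruitment was therefore continued according to the randomization lists, finally leading to 153 patients in each group, respectively". The article does not say how many patients were randomized to each arm, or how many did not commence and why.
- **Analysis set (Principles of the analyses).** "All analyses within the scope of the SPIZ evaluation are carried out in the intention-to-treat population". The same section leaves individuals with missing values out of the analysis concerned. It does not say whether randomized patients who never commenced belong to the set.
- **Allocation (Enrollment, randomization and patient pathway).** Assignment is 1:1 from permuted-block lists by age group within each of three centers. The result is shown to study staff once consent and eligibility are recorded.
- **Endpoint (Hypotheses and outcomes).** Death or unplanned disease-related rehospitalization, tested at 12 months after cellular therapy.

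**The concern.** Under intention-to-treat a patient belongs to the trial from randomization. A patient who never reaches the first outpatient visit is still analysed in the allocated arm, so there is nothing to make up for. Continuing recruitment because too few intervention patients had commenced makes sense only if those who commenced are regarded as the study population. That is a different population from the one promised under Principles of the analyses.

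The difference matters because the milestone can depend on the outcome. A patient who dies between randomization and the first visit has a primary endpoint event and cannot commence. A patient who deteriorates in that interval may also fail to commence. Staff know the allocation by then, and only one arm is asked to take up an app, home visits and video consultations. If the final 153 vs 153 became the primary analysis set, such patients would be missing from it and the comparison would no longer be the randomized one. Blinded adjudication of events cannot restore patients who are not in the set. The missing-data rule offers a second route to the same loss if no outcomes are retrieved for them.

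**Working it through.** **1. The planned total.** Under Sample size the article gives 143 per arm and 5% drop-out: (143 + 143)/0.95 = 286/0.95 = 301.05, rounded up to 302. This step reproduces. (The 143 itself does not follow from 55% vs 35% at one-sided 5% and 80% power, for which exact Fisher needs 85 per arm. That is a separate matter and does not bear on this point.)

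**2. What was counted.** 149 + 153 = 302, exactly the planned total. The two figures are described as patients who reached commencement, so the target was counted at that milestone. Recruitment then moved from 149/153 to 153/153. Both arms already exceeded the 143 that the plan required.

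**3. What omission could do.** The number of non-commencers is not stated, so this is an assumed range.

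Inputs:
- Test: "The case number calculation was performed with a one-sided Fisher test".
- Level: "Given a significance level of 5% and a yielded power of 80"%.
- Event rate: "a rehospitalisation rate of 55% after alloHCT in a German population", the article's control rate, used here in both arms so that there is no true effect.
- Analysed: 153 per arm.
- Assumed: *m* further randomized SPIZ patients are left out, with event rate *q*, and no control patients are left out.

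The event rate among the SPIZ patients who remain is

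p = (0.55 × (153 + m) − q × m) / 153.

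For m = 4 and q = 1: (86.35 − 4)/153 = 0.538. For m = 8 and q = 1: (88.55 − 8)/153 = 0.526. The rejection probability is the exact one-sided Fisher probability at 153 vs 153, by full enumeration, with 0.55 in controls and p in SPIZ.

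| m | q | p | Spurious difference (points) | Type I error |
|---|---|---|---|---|
| 0 | – | 0.550 | 0 | 3.7% |
| 4 | 55% | 0.550 | 0 | 3.7% |
| 4 | 80% | 0.543 | 0.7 | 4.8% |
| 4 | 100% | 0.538 | 1.2 | 5.8% |
| 8 | 55% | 0.550 | 0 | 3.7% |
| 8 | 80% | 0.537 | 1.3 | 6.1% |
| 8 | 100% | 0.526 | 2.4 | 8.6% |

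**4. A hypothetical borderline result.** 68/153 in SPIZ vs 84/153 in control gives one-sided p = 0.043. Restoring two omitted SPIZ patients with events (70/155) gives p = 0.055. Restoring four (72/157) gives p = 0.070.

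**The case against.** **No exclusion is stated.** The article promises intention-to-treat, and nothing in it limits the primary analysis to 153 vs 153. Continued recruitment adds patients and removes nobody. The exact analysis set is often left to the analysis plan, which exists but is not shown, and CONSORT reporting is promised. This stands in part: actual exclusion is not shown. It does not remove the conflict, because the article already gives 153 per arm as its group sizes and gives failure to commence as the reason for recruiting more.

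**The sum has another reading.** Exactly 302 patients might have been randomized and all have commenced, so that 149/153 is only chance imbalance. The wording about how few intervention patients reached commencement fits this poorly, but only the numbers randomized can settle it.

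**Several stronger inferences are tempting and not supported:**

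- *Loss was greater in the SPIZ arm, and the bias favours SPIZ.* Incomplete blocks in six center-by-age strata can produce a gap of four, and controls may have failed to commence too. Omitting controls who had events would work against SPIZ.
- *The arms faced different hurdles.* Data collection and management counts delivery as begun only when, among other conditions, the participant "has used at least one component of the SPIZ intervention". That rule concerns delivery of the intervention and stands among the fidelity measures. Nothing says that it produced the 149/153 count.
- *The top-up of four intervention and no control patients points to irregular allocation.* These are counts of patients who commenced, not of allocations, and they come from stratified permuted blocks.
- *Non-commencers were substituted one for one, or the 5% allowance was meant to cover them.* The article describes continued recruitment along the lists and does not define drop-out.

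**The calculation is one-sided by construction.** It assumes omissions from SPIZ only. With four omitted at an 80% event rate the error is 4.8%, still under the nominal 5%.

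**Conclusion.** The point holds as an inconsistency that puts the primary comparison at risk; bias has not been demonstrated. Accrual was counted, and its end decided, on a milestone reached after randomization and after open allocation, while the article promises intention-to-treat without tying it to all randomized patients.

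If every randomized patient is analysed with outcomes retrieved, no harm follows from how accrual was counted. If the 153/153 set is used, size and direction are unknown. Under the assumptions above (55% in both arms, omissions only from SPIZ) the type I error runs from 3.7%, when omission is unrelated to outcome, to 5.8% with 4 or 8.6% with 8 omitted patients who all had events. The calculation takes the confirmatory Fisher test as one-sided, as in the sample size section.

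**What to change.** Before results are known (the article expects the first in mid-2027):

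1. State that the primary intention-to-treat set is every randomized patient in the allocated arm, whether or not study commencement or onboarding took place.
2. Assess the primary endpoint in all of them over the window already fixed under Hypotheses and outcomes, to 12 months after cellular therapy. No new time origin is needed.
3. Retrieve vital status and readmissions for non-commencers from hospital records where consent allows, so that the missing-data rule does not remove them.
4. Report numbers randomized and numbers not commenced per arm, with reasons.
5. Keep the commenced set (153/153) as a sensitivity analysis only.

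The cost is a change of wording, a little data retrieval, and slight dilution of the effect estimate by patients who received none of the intervention. Made now, the choice cannot be read as driven by the data.
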